### Statistical analysis

Statistical analyses will be conducted on an intention-to-treat basis, but secondary analyses will be performed, including only those considered adherent to the protocol. Baseline characteristics will be presented using descriptive statistics to compare both groups.

According to the type and distribution of variables, between-groups differences will be evaluated using adequate tests. Continuous variables will be analyzed by t tests (for symmetrically distributed data), or Mann-Whitney U tests (for asymmetrical data). Categorical

[figure not shown]

**Table 2** Stages of training routines during pregnancy according to week of intervention

| Weeks of intervention | Warm-up | Aerobic exercise | Strength training/Floor exercises | Stretching |
|-----------------------|---------|------------------|-----------------------------------|------------|
| 1 to 4, Stage 1       | 5 min   | 15 min           | 35 min (sets: 3 × 12 repetitions) | 5 min      |
| 5 to 10, Stage 2      | 5 min   | 20 min           | 30 min (sets: 3 × 10 repetitions) | 5 min      |
| 11 to end, Stage 3    | 5 min   | 25 min           | 25 min (sets: 3 × 8 repetitions)  | 5 min      |

variables will be analyzed with chi-square tests or Fisher's exact test, as appropriate. General linear model or logistic regression will be employed to control for confounding factors. More specifically, based on the perinatal study information, preterm birth, gestational diabetes and eclampsia incidences will be compared in the two groups using chi-square tests, followed by multivariable analyses when adequate; linear regressions will be carried out to evaluate potential differences in birth weight, gestational weight gain and lipid profile. Analysis will be carried out in the statistical package STATA 12.0 (StataCorp, [name]) and significance will be set at 5 %.

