## Abstract

**Background:** Preterm birth is associated with most cases of neonatal deaths and negative health outcomes, and hypertensive disorders. Hypertension is influenced by maternal behavior, such as physical activity. Physical activity is associated with better outcomes for mother and fetus, besides healthier weight gains during pregnancy. Few women are physically active during pregnancy and few clinical trials have been carried out with pregnant women. The aim of this paper is to describe the protocol of a controlled trial evaluating whether regular exercise during pregnancy may result in improved maternal-child health and neonatal outcomes.

**Methods/Design:** The PAMELA (Physical Activity for Mothers Enrolled in Longitudinal Analysis) trial is a randomized controlled trial nested in a birth cohort study. Eligible women belonging to the birth cohort will be invited (between the 16th and 20th week of gestation) to enroll in the trial. Baseline data (blood and urine samples, anthropometry and pulmonary function) will be collected at enrollment. The same assessments will be repeated eight and 16 weeks after baseline. After randomization, women will be allocated into either one of these groups: control, 426 women who will be advised to keep their usual daily activities; and intervention, 213 women who will engage in an exercise program, three sessions a week. At least 70 % attendance over 16 weeks will be required to be considered compliant to the intervention. Exercise protocol will include aerobics, strength and flexibility training. Maternal and child outcomes will be measured at the 36th week of gestation, at birth and at three, 12, 24 and 48 months postpartum. An intention-to-treat analysis will be performed.

**Discussion:** Few women are active during pregnancy and a vast majority decrease their activities or even quit exercising. We present a population-based regular exercise intervention focused on the prevention of hypertension, pre-eclampsia and preterm birth. Data on the underlying cohort will allow future analysis using different outcomes with low probability of recall bias or misclassification of exposure status. Results will potentially influence prenatal care counseling in regards to physical activity.

**Trial registration:** Clinicaltrials.gov identifier: NCT02148965, registered on 22 May 2014.

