### Randomization

Pregnant women meeting the inclusion criteria and who agree to participate in the randomized controlled trial will be allocated randomly into either the intervention or control group. The randomization process will be done in blocks of nine women using random software sampling. Each block will therefore result in the allocation of three women for the intervention and six women for the control group, ensuring a recruitment balance of 1:2 throughout the study. This ratio was chosen as it would minimize costs and behavioral changes in women from the remaining cohort, whilst assuring that statistical power would be unaffected. As the cohort is an observational study, our option was to expose the lowest possible number of women to the intervention. After randomization, women will be allocated into either one of these groups: control, 426 women who will keep their usual daily activities; and intervention, 213 women who will engage in a physical activity program, three sessions a week.

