### Intervention procedures: exercise protocol

The intervention will start between the 16th and 20th week of gestation and will last 16 weeks. Workouts will be guided and supervised by a team of five previously trained physical education professionals. A set of exercises will be suggested for each workout, involving aerobic activities (treadmill or stationary bike), strength training (dumbbells, machines or elastic bands) and floor exercises. The intensity of the exercises will be set according to each woman's perceived effort (within the range of 12 to 14 on the Borg Scale) [25], and will be altered according to the progress of pregnancy. The workload will change according to the week of the intervention, and the stages are described in Table 2.

Each session will last around 60 min, and will include aerobic exercises (treadmill or stationary cycling), strength training (with focus on major muscle groups and pregnancy-specific exercises to help alleviate low back pain, and work abdominal and pelvic floor muscles to prevent urinary incontinence) and will end with stretching exercises. The exercises are described in the Table 3.

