### Primary outcome measures

Preterm birth (gestational age below 37 weeks of pregnancy), and pre-eclampsia (blood pressures above 140/90 mmHg and proteinuria above 15.0 mg/dL) will be assessed during pregnancy and soon after birth.

[figure not shown]

**Fig. 1** Study design

**Table 1** Exclusion criteria of the randomized controlled trial

| Exclusion criteria            | Description                                                   |
|-------------------------------|---------------------------------------------------------------|
| Age                           | Below 18 years                                                |
| Hypertension                  | Diagnosed before pregnancy/Self-reported                      |
| Diabetes                      | Diagnosed before pregnancy/Self-reported                      |
| Preterm birth                 | History of previous preterm birth                             |
| Miscarriage                   | History of previous miscarriage                               |
| Heart disease                 | Diagnosed before pregnancy/Self-reported                      |
| In vitro fertilization | Fertilization in the current pregnancy                        |
| Double/twin pregnancy         | Twin pregnancies confirmed by ultrasound                      |
| Persistent bleeding           | Women presenting persistent bleeding                          |
| Severe obesity                | Body mass index above 35 kg/m                     |
| Heavy smokers                 | Smoking more than 20 cigarettes a day                         |
| Active women                  | Weekly leisure-time physical activity > 150 min/Self-reported |

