### Follow-up and compliance to the study

To improve the follow-up rate, at the beginning of the study participants will be informed of the importance to attend all sessions, and the staff will register name and

contact information for follow-up on missed sessions to collect information on the reasons for the absence, and to offer women the opportunity to attend the session on a different day and/or time as soon as possible. Door-to-door transportation and a kit, containing a t-shirt, running tights and running shoes, will be offered for women in the intervention group. Both groups will be given study t-shirts and laboratory results around 10 days after collection. To be considered adherent to the intervention, women should attend 16 weeks of the program and a minimum of 34 (70 %) workout sessions, and cannot miss more than six training sessions in a row.

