### Control group

Women allocated to the control group will be instructed to continue their usual routines, will do the same assessments as the intervention group and will be followed by the 2015 Pelotas (Brazil) Birth Cohort Study.

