### Sample size calculation

For the sample size calculation, based on a statistical power of 80 %, a level of significance set at 5 % and using different outcomes from the last birth cohort [28] and estimates based on secular trends (preterm birth at 16 %, gestational hypertension at 18 %, leisure-time physical activity during pregnancy at 13 % and estimate of risk reduction with the intervention at 30 %), we estimated that 213 women would be necessary for the intervention group. The intervention:control ratio will be 1:2, therefore 426 will be included as the control group.

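### The adherent-only secondary analysis can never count a woman who delivers before her programme ends, so its preterm birth comparison leans towards benefit even if exercise has no effect

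*Protocol*

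**What the plan says.** All references are to the protocol. The main analysis is by intention to treat; in addition, "secondary analyses will be performed, including only those considered adherent to the protocol" (Statistical analysis).

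Adherence is fixed under Follow-up and compliance to the study: "women should attend 16 weeks of the program and a minimum of 34 (70 %) workout sessions", with no run of more than six missed sessions. The Abstract puts it more briefly: "At least 70 % attendance over 16 weeks will be required to be considered compliant to the intervention".

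On timing, "The intervention will start between the 16th and 20th week of gestation and will last 16 weeks" (Intervention procedures: exercise protocol). The frequency is three sessions a week (Randomization).

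One of the two primary outcomes is "Preterm birth (gestational age below 37 weeks of pregnancy" (Primary outcome measures). On the other side, "Women allocated to the control group will be instructed to continue their usual routines" (Control group). No section sets an adherence condition for controls that depends on staying pregnant to a given week.

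**The concern.** Adherence can be judged only at the end of a 16-week window, and the woman must still be pregnant then. That window lies wholly before 37 weeks. A preterm delivery inside it makes the woman non-adherent automatically, whatever her attendance up to that day. The analysis thus removes some intervention women because they had the primary outcome and keeps their counterparts in the control arm. This is immortal-time bias.

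At stake is the meaning of the secondary result for preterm birth: a risk ratio below 1 could come from the exercise, from the selection rule, or from both, and the analysis could not separate them. Adjusting for baseline covariates does not help, because the selection is on the outcome itself.

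**Working it through.** **Inputs from the protocol**
- Programme start at week 16–20, length 16 weeks (Intervention procedures).
- Three sessions a week; 213 intervention and 426 control women (Randomization).
- Adherence: 16 weeks and at least 34 sessions (Follow-up and compliance).
- Preterm limit: 37 weeks (Primary outcome measures).
- Preterm rate p = 0.16, from "preterm birth at 16" per cent; planned risk reduction 30% (Sample size calculation).

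**Inputs assumed, because the protocol does not give them**
- s, the share of preterm births that occur before the woman's own programme end, shown from 0.10 to 0.60.
- Adherent women are compared with all controls.
- Non-adherence for other reasons is unrelated to preterm birth.

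**1. The protocol's own adherence figure.** 16 × 3 = 48 sessions. 0.70 × 48 = 33.6, rounded up to 34, and 34/48 = 70.8%. The stated 34 (70%) is reproduced, and its denominator is the full 16 weeks, not the sessions available before delivery.

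**2. Programme end.** 16 + 16 = 32 weeks at the earliest and 20 + 16 = 36 weeks at the latest. Both are below 37, so every delivery before programme end is a preterm birth.

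**3. Risk ratio under no effect.** Let the true preterm risk be p in both arms. Among intervention women a fraction p·s deliver preterm before programme end and cannot be adherent. Among the rest, the preterm risk is

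q = p(1−s) / (1−ps), so the apparent RR = q/p = (1−s) / (1−0.16s).

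As a count at s = 0.30: 213 × 0.16 = 34.1 preterm births; 0.30 × 34.1 = 10.2 are removed; (34.1 − 10.2)/(213 − 10.2) = 23.9/202.8 = 11.8%, against 16% in controls.

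| s (assumed) | q, adherent women | RR with no true effect | False reduction |
|---|---|---|---|
| 0.10 | 14.6% | 0.915 | 9% |
| 0.15 | 13.9% | 0.871 | 13% |
| 0.20 | 13.2% | 0.826 | 17% |
| 0.30 | 11.8% | 0.735 | 26% |
| 0.60 | 7.1% | 0.442 | 56% |

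**4. Where the artefact equals the planned effect.** Setting (1−s)/(1−0.16s) = 0.70 gives s = 0.30/(1 − 0.112) = 0.34.

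**5. Chance of a falsely significant benefit.** Assume also that 70% of the women not removed by early delivery adhere, so n₁ = 213 × (1−0.16s) × 0.7, compared with 426 controls at two-sided 5%. The approximation is Φ[(p − q − 1.96·SE₀)/SE₁], with SE₀ from the pooled and SE₁ from the separate proportions.

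| s | n₁ | Approximation | Simulation (40,000 runs) |
|---|---|---|---|
| 0.10 | 147 | 5.5% | 5.3% |
| 0.20 | 144 | 11.4% | 11.1% |
| 0.30 | 142 | 21.7% | 21.9% |

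Without the selection (s = 0) the simulated figure is 2.2%, close to the nominal 2.5%.

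**6. A looser reading of the rule.** If only the 34-session minimum counted, 34/3 = 11.3 weeks would still be needed. Women delivering before about week 27 (16 + 11.3) to week 31 (20 + 11.3) would still be excluded. The bias shrinks but remains.

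**The case against.** Intention-to-treat is the main analysis, and the protocol labels the adherent-only work secondary. The randomised comparison, the sample and the data are untouched. This stands, and it limits the severity.

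The protocol does not say which outcomes the adherent-only analyses cover or how their control group is formed, and an analysis plan that is not at hand might settle both. This stands as a condition on the size. It does not excuse the adherence rule, which the protocol itself fixes with no exemption for early delivery.

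Four stronger readings are tempting and are not supported:
- *That adherence is defined by not having the outcome.* Only part of the outcome is excluded. A woman who starts at week 16 finishes at week 32 and can then deliver before 37 weeks as an adherent preterm case.
- *That the false reduction is always at least the planned 30%.* At s = 0.15 and 0.30 it is 13% and 26%; it passes 30% only above s of about 0.34, and the documents do not give s.
- *That women with pre-eclampsia are removed in the same way.* Such women might stop attending and so fail the rule, but no section says that they do. That would be informative dropout, which is possible but not definitional.
- *That the biased result will be the one emphasised.* Nothing in the protocol says how the two results will be weighed in reporting.

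**Conclusion.** The point holds for preterm birth in the adherent-only secondary analysis. The direction follows from the protocol's own timing and adherence rule: for any s above zero, and adherent women set against all controls, the expected risk ratio is below 1 when exercise does nothing. The size is conditional. It runs from a mild distortion (RR about 0.91 at s = 0.10) to a severe one (0.44 at s = 0.60), and rests on the 16% rate, the assumed s, and other non-adherence being unrelated to the outcome.

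Outcomes tied to length of gestation, such as birth weight, may be shifted in the same direction; that was not quantified. A reader might infer that the trial's main conclusion is compromised; it is not, because intention-to-treat keeps all women as randomised. The rating is should-fix.

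**What to change.** Keep intention-to-treat as the primary analysis, and change the secondary analysis as follows:
1. Do not use the current adherent-only set for preterm birth or other gestation-dependent outcomes.
2. For analysis, define adherence as sessions attended divided by sessions scheduled while the woman is still pregnant, so that early delivery does not by itself make her non-adherent.
3. Estimate the effect of adherence with randomised allocation as the instrument, keeping every randomised woman. On the risk-difference scale this is (p_I − p_C)/a, where p_I and p_C are the preterm risks in all women randomised to intervention and control, and a is the difference between arms in the share adhering. With p_I = p_C = 0.16 it is 0, so the artefact disappears. Using the new definition merely to restrict the sample would remove the definitional exclusion, but not any dropout linked to illness.

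The cost is a change of wording and modest extra analysis; missed sessions are already followed up. There are two downsides. The interval will be wider than for the adherent-only contrast. The complier estimate also assumes that partial attendance among women classed as non-adherent has no effect; this should be stated and examined in a sensitivity analysis, for example by varying the adherence threshold.

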## Aim

The aim of this study is to present the experimental protocol of a trial aimed at evaluating the effectiveness of an exercise intervention, by comparing the intervention and control groups with infant outcomes assessed later in life. Data will be collected on: prematurity, gestational age, gestational weight gain, blood pressure, fasting blood glucose, postpartum weight retention, postpartum depression and birth weight.

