### Secondary outcome measures

Secondary outcomes will be assessed during pregnancy and until children reach the age of 48 months, specifically: blood lipid profile, lung function (peak expiratory flow - nSpire Health PiKo-1® - nSpire Health, Inc. - [name]), gestational diabetes (self-reported, by the time of delivery), gestational weight gain (calculated based on pre-gestational weight and weight at admission to deliver), mode of delivery (vaginal or cesarean section), birth weight (in grams), length at birth (in cm) and fetal growth (according to the new Intergrowth-21st fetal growth curves [26]). At three months post-partum two outcomes will be measured: post-partum weight retention (difference between current weight and pre-gestational weight) and depression (measured by the Edinburgh Postnatal Depression Scale). Infant neurodevelopment will be assessed (measured by the Battelle Developmental Inventory) at the 12, 24 and 48-month visits [27].

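### Infant neurodevelopment is scored at 12, 24 and 48 months, but the only stated rule that reaches a continuous score tests each age alone; one mixed model would use the scores a little better when visits are missed

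*Protocol*

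**What the plan says.** The protocol's Secondary outcome measures section states: "Infant neurodevelopment will be assessed (measured by the Battelle Developmental Inventory) at the 12, 24 and 48-month visits". The Aim section describes evaluating the intervention "by comparing the intervention and control groups with infant outcomes assessed later in life".

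The Statistical analysis section gives one general rule for continuous data: "Continuous variables will be analyzed by t tests (for symmetrically distributed data), or Mann-Whitney U tests (for asymmetrical data". Two further sentences concern models. One is for adjustment: "General linear model or logistic regression will be employed to control for confounding factors". The other assigns a method to named outcomes: "linear regressions will be carried out to evaluate potential differences in birth weight, gestational weight gain and lipid profile". Neurodevelopment is not among those outcomes. No mixed model, estimating-equation or other repeated-measures method is named. The protocol does not say how the Battelle scores are scaled, whether one age takes priority, or what happens when a visit is missed.

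**The concern.** Three scores from one child are correlated, and follow-up to 48 months will lose some children at some visits. A two-sample test at 48 months uses only the children who attended then. A child scored at 12 and 24 months but absent at 48 contributes nothing to the 48-month comparison, although the two earlier scores carry information about the missing one.

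The stakes are some precision at the later ages and a stronger condition on missed visits. Tests restricted to each visit's attenders make no allowance for attendance that depends on earlier scores. A likelihood-based longitudinal model does.

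**Working it through.** **Inputs.** Arm sizes of 213 and 426 come from the Sample size calculation section. The protocol sizes the trial on binary outcomes, so it has no figure for neurodevelopment to reproduce. The variance ratios below do not depend on the arm sizes.

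Assumed, because the protocol gives none of them: a score standardised to SD 1; equal within-child correlation ρ of 0.3, 0.5 or 0.7; retention at 12/24/48 months of 90/85/80% or 85/75/65%, the same in both arms and random; and, for power, a difference of 0.20 SD at a two-sided 5% level.

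**1. One age, complete data.** SE = √(1/213 + 1/426) = √0.00704 = 0.0839 SD. Power for 0.20 SD = Φ(0.20/0.0839 − 1.96) = 66%. The difference with 80% power is (1.96 + 0.8416) × 0.0839 = 0.235 SD. With all three scores present, the mixed model with arm-by-visit terms gives the same variance for an age-specific difference (ratio 1.00).

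**2. The 48-month difference with missed visits.** Variances are in units of 1/213 + 1/426. The separate test has variance 1/r₃, where r₁, r₂, r₃ are the retained fractions.

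Permanent dropout: the model variance is (1 − R²)/r₃ + (R² − ρ²)/r₂ + ρ²/r₁, with R² = 2ρ²/(1 + ρ). At ρ = 0.5, R² = 0.3333. With 90/85/80% this gives 0.6667/0.80 + 0.0833/0.85 + 0.25/0.90 = 0.8333 + 0.0980 + 0.2778 = 1.209. The separate test has 1/0.80 = 1.250, so the ratio is 0.967.

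Independently missed visits: sum, over attendance patterns, the pattern's probability times the inverse covariance of the scores observed. Invert the total and take the 48-month element. At ρ = 0.5 and 90/85/80% this is 1.172, a ratio of 0.938.

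Variance ratio at 48 months, model to separate test:

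| Retention | Missed visits | ρ = 0.3 | ρ = 0.5 | ρ = 0.7 |
|---|---|---|---|---|
| 90/85/80% | independent | 0.975 | 0.938 | 0.890 |
| 90/85/80% | permanent dropout | 0.987 | 0.967 | 0.940 |
| 85/75/65% | independent | 0.959 | 0.897 | 0.814 |
| 85/75/65% | permanent dropout | 0.972 | 0.930 | 0.873 |

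In power terms, at 90/85/80% and ρ = 0.5, the separate 48-month test has SE 0.0839/√0.80 = 0.0938 and 57% power for 0.20 SD. The model has SE 0.0839 × √1.172 = 0.0909 and 60% if visits are missed independently, or 0.0839 × √1.209 = 0.0923 and 58% under permanent dropout.

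**3. The average over the three ages, complete data.** SE = 0.0839 × √((1 + 2ρ)/3) = 0.0613, 0.0685, 0.0751 for ρ = 0.3, 0.5, 0.7. If the effect is 0.20 SD at every age, power is 90, 83 and 76%. If it is 0.20 SD at 48 months only, the average is 0.20/3 = 0.067 SD, and power at ρ = 0.5 is Φ(0.067/0.0685 − 1.96) = 16%. If it is present at 24 and 48 months, the average is 0.133 SD and power is 49%.

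**The case against.** The strongest objection is that the protocol names no analysis for neurodevelopment. The general rule is introduced with reference to the type and distribution of each variable, and the sentence on specific outcomes concerns perinatal data. The modelling of a three-visit secondary outcome is often left to the SAP, which is not shown and may already contain a longitudinal model. The protocol does not say that the Battelle score will be treated as continuous, and the Aim section's list of data to be collected omits neurodevelopment. All of this stands and limits the weight of the point. It does not remove it, because the protocol states a rule for continuous variables that, as written, yields separate tests at each age.

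Three stronger readings are tempting, and the documents support none of them.

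- A reader might set 66% power for one age against 83% for the three-age average and infer that much power is thrown away. Those are different estimands. The second figure assumes the same effect at every age, and the protocol never names an average as its target. For the same age the gain is nil with complete data and small otherwise.
- A reader might infer that the per-visit tests are invalid unless attendance is unrelated to development. That is too strong. If attendance depends on development in the same way in both arms, the two-arm test remains valid under the null. Dependence on measured covariates can be addressed with the general linear model that the protocol allows.
- A reader might infer that a child who misses a visit is lost altogether. The child is lost only from that visit's comparison.

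**Conclusion.** The point holds as a modest one about a secondary outcome. The stated rule analyses each age in isolation and leaves earlier scores unused when a later visit is missed. The loss of precision at 48 months is about 2 to 11% of variance at 90/85/80% retention if visits are missed independently, and about 1 to 6% under permanent dropout. At 85/75/65% the ranges are about 4 to 19% and 3 to 13%. These figures rest on assumed retention, an assumed equal correlation of 0.3 to 0.7 and randomly missed visits, so they measure efficiency only; no bias has been quantified.

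The second benefit is qualitative: validity when missed visits depend on observed earlier scores. The case for change rests on its low cost. It does not support making the three-age average the main neurodevelopment result.

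**What to change.** In the Statistical analysis section, state that Battelle scores, if analysed as continuous, will be analysed in one linear mixed model with arm, visit and arm-by-visit terms and an unstructured within-child covariance, including every child with at least one score. Report the arm difference at 12, 24 and 48 months from that model.

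The average over the three ages may be added as a supplementary summary if the scores are on a comparable scale. It is more precise only if the effect is similar across ages, and it should not replace the age-specific results.

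The cost is a sentence or two of protocol text and slightly more analysis work, with no new data or visits. The downside is reliance on a missing-at-random assumption, which should be stated. If the SAP already specifies such a model, the protocol need only be brought into line with it.

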## Rationale

Although early studies on the effects of leisure-time physical activity during pregnancy were concerned about potential harmful effects to the health of the mother and the fetus, these have not been proven over time [21]. Current guidelines suggest that pregnant women should engage in at least 30 min of moderate-intensity physical activity on most, if not all days of the week, in the absence of medical or obstetric complications, in agreement with the recommendations for healthy adults [22].

Today, there is growing evidence supporting the association of safe physical activity during pregnancy with benefits to maternal and child health [23, 24]. However, most of the scientific evidence derives from observational studies, and there is a need for well-designed experimental studies that enable a better understanding on the impact of exercise during pregnancy on various maternal and mother-child health outcomes.

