### Logistics and setting

The study begins with one initial contact with the mother, prior to the 16th week of gestation, when interviewers ask for contact information, conduct a brief interview and hand a leaflet explaining the controlled trial. After enrollment in the study, women will be invited to go to the Epidemiology Research Center to collect baseline data, that is, blood and urine sampling, anthropometry, blood pressure and lung function. The same assessments (in both groups) will be repeated at eight and 16 weeks

after baseline. The facilities of the Federal University of Pelotas at the Physical Education School will be used for the intervention. A second interview at hospital will take place soon after birth (when children will be measured and mothers will be asked about many aspects of their pregnancy). After these initial data collections, when children are three, 12, 24 and 48 months, interviews will be carried out at the Epidemiologic Research Center or the participant's household. Fig. 2 shows the recruitment flowchart and subsequent data collections.

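### No outcome counts fetal loss, stillbirth or neonatal death by arm, and the preterm comparison may omit pregnancies lost before the hospital birth interview

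*Protocol*

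**What the plan says.** **Outcomes.** Under *Primary outcome measures* the protocol names pre-eclampsia and "Preterm birth (gestational age below 37 weeks of pregnancy"), and says both "will be assessed during pregnancy and soon after birth". The birth outcomes under *Secondary outcome measures* are "mode of delivery (vaginal or cesarean section), birth weight (in grams), length at birth (in cm) and fetal growth". Neither list, nor the data list under *Aim*, includes miscarriage, stillbirth, fetal death or neonatal death.

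**Safety.** *Ethical considerations* provides for referral of women who develop health problems. No comparison of adverse events between arms is described.

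**Exposure.** "The intervention will start between the 16th and 20th week of gestation and will last 16 weeks".

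**Data source and population.** *Statistical analysis* states "Statistical analyses will be conducted on an intention-to-treat basis", and then that "based on the perinatal study information, preterm birth, gestational diabetes and eclampsia incidences will be compared in the two groups". *Logistics and setting* describes the data collection at birth: "A second interview at hospital will take place soon after birth". The child is measured and the mother is asked about her pregnancy.

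**Context.** The *Abstract* and *Background* use neonatal death to explain why preterm birth matters. *Rationale* notes that early studies "were concerned about potential harmful effects to the health of the mother and the fetus", and adds in the same sentence that such harm has not been proven. *Discussion* expects the results to be used in routine prenatal counselling.

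**The concern.** There are two linked problems.

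1. **Deaths are not an outcome.** The trial tests an exposure during pregnancy and is meant to inform routine advice. As written, a difference between arms in fetal or neonatal deaths would not be reported, because no outcome counts these events.

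2. **The primary comparison may depend on reaching the birth interview.** Fetal loss competes with preterm birth, since a pregnancy that ends in loss cannot later end in a live preterm birth. If women without a birth interview are left out, and losses differ between arms, the preterm comparison is distorted. More losses with exercise would look like fewer preterm births with exercise.

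**Working it through.** The plan gives no loss rate, so it has no figure of its own to reproduce here. The arithmetic below illustrates size only.

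**Inputs from *Sample size calculation*:** 213 intervention and 426 control women, 16% preterm birth, and a 30% risk reduction as the planned effect. **Assumed:** every loss rate *L* below.

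**Two ways to read the text**

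| Reading | Effect on the preterm comparison | Are deaths shown by arm? |
|---|---|---|
| A loss without a birth interview is left out | Woman leaves numerator and denominator | No |
| Any end of pregnancy before 37 weeks counts as preterm birth | Woman counted, but a loss at 20 weeks equals a live birth at 36 | No |

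The protocol does not say which reading applies. Deaths go unreported under both.

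**Expected number of losses.** With *L* from 0.5% to 3%: 213 × 0.005 = 1.1 to 213 × 0.03 = 6.4 in the intervention arm, and 426 × 0.005 = 2.1 to 426 × 0.03 = 12.8 in the control arm.

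**Case A: loss or birth before 37 weeks is truly 16% in both arms, and losses are left out.** Observed preterm rate = (0.16 − *L*) / (1 − *L*).

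| *L* exercise | *L* control | Observed exercise | Observed control | Risk ratio (truth 1.00) |
|---|---|---|---|---|
| 1% | 1% | 0.15/0.99 = 15.2% | 15.2% | 1.00 |
| 2% | 1% | 0.14/0.98 = 14.3% | 15.2% | 0.94 |
| 3% | 1% | 0.13/0.97 = 13.4% | 15.2% | 0.88 |
| 4% | 2% | 0.12/0.96 = 12.5% | 14.3% | 0.87 |
| 1% | 3% | 15.2% | 13.4% | 1.13 |

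At 3% against 1%, the false reduction is about 12%, over a third of the planned 30%. The last row shows that the bias reverses if losses are higher in control.

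**Case B: 16% of the remaining births are preterm in both arms, and losses of 3% (exercise) and 1% (control) come on top.** The births-only comparison shows 16.0% in each arm. Counting loss or birth before 37 weeks in all randomised women gives 0.03 + 0.97 × 0.16 = 18.5% against 0.01 + 0.99 × 0.16 = 16.8%, a risk ratio of 1.10.

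**What the trial could test.** By a normal approximation, which is rough at such small counts, two-sided power to detect a difference in losses is about 20% for 2% against 1%, 33% for 4% against 2%, and 47% for 3% against 1%. For the Case B composite, the standard error is √(0.185 × 0.815/213 + 0.168 × 0.832/426) ≈ 3.2 points for a 1.7-point difference, so power is about 8%.

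**The case against.** The strongest reply is that a reader might infer that lost pregnancies are dropped from the analysis, and the protocol nowhere says so. It states intention to treat. Its definition of preterm birth has no live-birth restriction and no lower gestational limit. It also says the primary outcomes are assessed during pregnancy as well as after birth. A stillbirth before 37 weeks could therefore already count as an event. **This stands:** omission is a possibility created by the stated data source, not a stated rule.

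A reader might also infer that neonatal deaths leave the preterm comparison. They do not, because the gestational age at a live birth is known. They are only uncounted as deaths. That later infant development is measured in survivors is unavoidable and is no fault of the plan.

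It can be said that losses would come to light anyway. Both arms are reassessed eight and 16 weeks after baseline, missed sessions are followed up for reasons, and controls are followed by the cohort. This stands in part. None of these contacts creates a comparison by arm, and only the intervention arm has sessions to miss, so losses may become known more readily there.

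The counting rule may sit in an analysis plan that is not shown, and its absence alone would be no finding. But the outcome list and the data source for the primary comparison are set in the protocol. An analysis plan cannot recover deaths that were never systematically ascertained.

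Finally, the protocol excludes women with a previous miscarriage, a previous preterm birth or persistent bleeding, which may make losses fewer. It also says that fetal harm has not been proven. Both are fair. Neither removes the reason to count deaths in a trial meant to guide counselling.

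**Conclusion.** The point holds in two parts of different certainty.

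- **Certain from the text:** no listed outcome counts fetal loss, stillbirth or neonatal death, and no comparison of harms by arm is described. A difference in deaths would go unreported however preterm birth is counted.
- **Possible from the text:** because the comparison rests on data collected around birth, women who lose a pregnancy without a birth interview may be left out, contrary to intention to treat.

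The size of any bias rests wholly on assumed loss rates and on losses that differ between arms. With losses of 1–2% in control and 2–4% with exercise, a true risk ratio of 1.00 would appear as about 0.87 to 0.94. Equal losses leave the ratio unchanged. The documents do not support a claim that the trial will be biased, or that exercise causes losses. The gap should be closed, but it does not invalidate the design.

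**What to change.** - **Primary outcome measures:** keep preterm birth as the primary outcome. Making the composite primary would change the question the trial asks, and is not needed.
- **Secondary outcome measures:** add fetal loss/stillbirth and neonatal death, reported as counts and percentages by arm. State that the outcome of every randomised pregnancy is ascertained in the same way in both arms, through the contact details and cohort follow-up already in place, including for women with no birth interview.
- **Statistical analysis:** add a prespecified companion analysis with fetal loss or birth before 37 weeks as the event and all randomised women in the denominator. State how a loss before 37 weeks counts in the primary comparison.

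**Cost:** a few sentences, a small number of extra contacts (about 3 to 19 losses in total at assumed rates of 0.5% to 3%, from 639 × 0.005 to 639 × 0.03), and one extra analysis. Power to test a difference in losses will be low, so these results should be labelled descriptive. Even no losses among 213 exercising women would rule out only rates above about 1.4% (one-sided 95% limit, 1 − 0.05^(1/213)).
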